3.6 Test Indicators and Methods

The physical health indicators were tested according to the "National Physical Fitness Standards for Students (2014 Revision)," including body shape, cardiorespiratory endurance, speed, strength, flexibility, and muscular endurance. The body composition indicators were assessed using body mass index (BMI) and waist circumference. Cardiorespiratory endurance was tested using vital capacity. Strength was measured by a 1-minute sit-up test (female) or pull-up test (male). Speed was measured using the 50-meter run. Flexibility was tested using the sit-and-reach test. Muscular endurance was measured with an 800-meter run (female) or 1000-meter run (male). The main testing methods are as follows:

1) Body Mass Index (BMI): The participant stands barefoot on a height measuring platform with their back against the column, feet together, and body straight. The participant's heels, sacrum, and scapula should be in contact with the column, with the head aligned horizontally. The height is recorded in centimeters (cm), accurate to one decimal place. Weight is recorded in kilograms (kg), also accurate to one decimal place. BMI is calculated using the formula: BMI = weight / height² (kg/m²).

2) Vital Capacity: A dry, disposable mouthpiece (or disinfected non-disposable mouthpiece) is used. The participant should take a deep breath and exhale into the mouthpiece until no more air can be expelled, avoiding inhalation during the test. The final reading on the LCD screen is recorded as the vital capacity in milliliters (mL), and the maximum value is selected as the result.

3) 1-Minute Sit-Up Test (Female) / Pull-Up Test (Male): For sit-ups, the participant lies on a mat with arms crossed over their chest, palms pressed against the shoulders, and feet flat on the ground, with knees at a 90° angle. Each sit-up is counted when the elbows touch or exceed the knees. The number of sit-ups performed in 30 seconds is recorded. For pull-ups, the participant grasps a horizontal bar with both hands shoulder-width apart, hanging with straight arms. After stabilizing their body, they pull up until the chin is above the bar, and the number of successful pull-ups is recorded.

4) Standing Long Jump: The participant stands with feet apart behind the take-off line, ensuring no part of the foot crosses the line. The distance from the take-off line to the nearest point of landing is measured, and the heel must land fully within the test area. The best of three jumps is recorded.

5) 50-Meter Sprint: A 50-meter straight track is marked on flat ground, and the time is recorded with a stopwatch. The test starts with the "Ready" command, and the participant begins running when the whistle is blown. Timing ends when the participant reaches the finish line.

6) Sit-and-Reach Test: The participant sits on the floor or mat with their back, hips, and shoulders against the wall, legs straight, and arms extended forward with palms facing down. The participant pushes the testing device forward as far as possible without bouncing, and the result is recorded in centimeters (cm).

7) 800-Meter Run (Female) / 1000-Meter Run (Male): The test is conducted on a 400-meter athletic track. The participant starts from a standing position, and timing starts upon hearing the starting gun and ends when the torso crosses the finish line. The result is recorded in minutes and seconds without decimals.

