Exclusion criteria: (1) Students with contraindications to physical activity; (2) Students with severe cardiovascular or musculoskeletal diseases; (3) Students who are sick, injured, have chronic diseases, are taking medication, or are in their menstrual period (female students); (4) Students who have not signed the informed consent form.

Criteria for removal: (1) Students absent for more than one-third of the sessions; (2) Students who are unable to complete the tests due to personal or family reasons; (3) Students who participated in other sports training sessions during the intervention, violating the intervention plan.

Mid-study withdrawal criteria: Students who transferred schools or could not continue participating in the study due to other reasons.

3.3Experiment Content

This study was primarily conducted in primary and secondary schools, involving six classes (approximately 300 students) who voluntarily participated. Three classes were designated as experimental groups, which adopted the Healthy Physical Education Curriculum Model of China for physical education instruction, while the other three classes served as control groups, receiving traditional physical education instruction.

The experimental groups underwent 12 weeks of physical education instruction based on the Healthy Physical Education Curriculum Model of China, whereas the control groups followed the conventional traditional physical education instruction for the same duration. Pre- and post-instruction assessments were conducted to measure the students' physical and mental health indicators. The physical health indicators were evaluated according to the National Student Physical Health Standard (Revised in 2014), which included anthropometric measurements, vital capacity, speed, strength, flexibility, agility, and other indicators. The mental health indicators were assessed through questionnaires, covering healthy behaviors, sportsmanship, depressive symptoms, and other indicators. Additionally, 40 students (20 from the experimental group and 20 from the control group) were randomly selected to provide 15 ml of urine samples before instruction, after the first session of instruction, and after 12 weeks of instruction. Non-targeted metabolomics techniques were employed to detect changes in metabolites within the body, in order to explore the underlying mechanisms by which exercise promotes health.

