3.10 Data Statistics and Analysis

Data will be analyzed using SPSS 26.0. Normality tests will be performed using the Shapiro-Wilk method, and data will be presented as mean ± standard deviation. Paired sample t-tests will be used to compare differences before and after intervention for each indicator. Independent sample t-tests will be used to compare baseline indicators between the two groups and differences between the pre- and post-intervention values. Statistical significance is set at P<0.05.

1. **Expected Timeline and Completion Dates**

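### Section 3.6 takes vital capacity as the measure of cardiorespiratory endurance and labels the 800/1000 m run as muscular endurance, so results on cardiorespiratory endurance would rest on a lung volume.

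*Protocol*

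**What the plan says.** Section 3.6 of the protocol lists six components of physical health, "including body shape, cardiorespiratory endurance, speed, strength, flexibility, and muscular endurance", and then assigns tests to them one by one. Two of these assignments matter here: "Cardiorespiratory endurance was tested using vital capacity" and "Muscular endurance was measured with an 800-meter run (female) or 1000-meter run (male".

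The same section describes how each test is done. For vital capacity (item 2) the student inhales deeply and blows out until empty: "The final reading on the LCD screen is recorded as the vital capacity in milliliters (mL), and the maximum value is selected as the result". For the 800/1000 m run (item 7) the student runs the distance on a track against the clock: "The result is recorded in minutes and seconds without decimals".

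Section 3.3 gives a second list of physical indicators, "which included anthropometric measurements, vital capacity, speed, strength, flexibility, agility, and other indicators". There vital capacity stands under its own name, and agility appears, which the 3.6 list does not contain. Item 4 of 3.6 describes a further test, "Standing Long Jump: The participant stands with feet apart behind the take-off line", which no assignment sentence links to a component.

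Section 3.10 sets out the analysis indicator by indicator: "Paired sample t-tests will be used to compare differences before and after intervention for each indicator". Changes are then compared between the groups by independent t-tests.

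**The concern.** The assignments in 3.6 are outcome definitions. They fix which component of fitness a result speaks to, and they stand in the measurement section of the protocol, so they are not a detail left for an analysis plan.

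Two of them do not fit the tests as described. A full exhalation at rest involves no sustained effort, so it cannot show how long or how well a student keeps up exercise. The distance run does involve sustained effort, but is filed under another component.

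What is at stake is the reading of the results. If run times improve and vital capacity does not, a report that follows 3.6 would say that muscular endurance improved and cardiorespiratory endurance did not. If vital capacity rises and run times do not change, the same report would claim a gain in cardiorespiratory endurance on the strength of a lung volume. Neither statement would follow from the data. Table 1 sets the exercise load by a heart-rate range (140-160 beats/min), so readers are likely to look for the cardiorespiratory result.

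**Working it through.** The plan gives no figure on this point, so there is nothing to reproduce by arithmetic. The check sets the components in 3.6 beside the tests described in 3.6 and the list in 3.3.

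| Component in 3.6 | Test assigned in 3.6 | What the described test records | Fit |
|---|---|---|---|
| Body shape / composition | BMI, waist circumference | Height and weight (item 1); no method given for waist | Fits |
| Cardiorespiratory endurance | Vital capacity | Volume of a full exhalation in mL, highest reading kept (item 2) | Does not fit: no sustained effort |
| Speed | 50 m run | Sprint time (item 5) | Fits |
| Strength | Sit-ups (girls) / pull-ups (boys) | Number of repetitions (item 3) | Acceptable |
| Flexibility | Sit-and-reach | Reach in cm (item 6) | Fits |
| Muscular endurance | 800 m / 1000 m run | Time for a continuous run (item 7) | Poor fit: sustained whole-body effort |
| (none) | Standing long jump | Jump distance (item 4) | No component given |

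Step 1. Cardiorespiratory endurance: the only test assigned is vital capacity. Item 2 describes no exercise and no duration. The result is a static volume.

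Step 2. Is a better test already in the battery? Of the seven numbered items, one is anthropometric, one is an exhalation, one counts repetitions, one is a jump, one is a short sprint and one is a reach. That leaves one sustained whole-body effort, the 800/1000 m run. The data needed are therefore already being collected, under another label.

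Step 3. Count: 2 of the 6 components in 3.6 carry a label that their test does not support.

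Step 4. Comparison of the lists: agility is in 3.3 but is not among the six components of 3.6, and none of the seven items is assigned to it. Of the seven items, six are linked to a component and one, the standing long jump, is not.

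Step 5. Effect on the analysis: section 3.10 tests each indicator separately. A relabelling leaves every measurement, mean difference and p-value as it was.

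**The case against.** The strongest reply is that the labels do little work. The objective speaks of physical and mental health levels in general, no endpoint or hypothesis is defined at component level, and 3.10 analyses indicators, not components. Section 3.3 already names vital capacity as itself, so a report could give the result in millilitres and never use the disputed label. The tests are said to follow a national standard (2014 revision) that is not at hand, and the labels may come from it. A sustained run also loads the leg muscles, so calling it muscular endurance is not empty.

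Much of this stands. It limits the point to wording and rules out any claim that the data or the tests are wrong. It does not rescue the two labels: 3.6 states them outright, and a report that follows 3.6 would use them. Nor would an outside origin make an exhalation volume a measure of endurance. That the run has some muscular component does not explain why it is kept away from the cardiorespiratory one.

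A reader might go further and infer several things that the documents do not support:

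- That agility is a declared outcome with no test at all. Section 3.6 says that it gives only the main methods, and it gives none for waist circumference, which it does name as measured. The description is therefore not complete, and an undescribed agility test cannot be excluded. In any case an outcome without data would yield no false conclusion. What is shown is that two lists disagree.
- That the standing long jump could be attached to whichever component suits the result. It is analysed as an indicator of its own, so this is speculation; only a label is missing.
- That filing sit-ups and pull-ups under strength is a mistake. That is a choice of classification.

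**Conclusion.** The point holds for the two endurance labels. Following 3.6, conclusions on cardiorespiratory endurance would rest on a static lung volume, while the one sustained run in the battery would be left out of them. That is 2 of the 6 components in 3.6. The disagreement between 3.3 and 3.6 over agility, and the long jump without a component, are secondary wording points.

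The size is modest: what each result may be said to show changes, and nothing in the data, the tests or the p-values does. It is still worth correcting before results are reported, because the labels decide how a positive or null finding is described.

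The conclusion assumes that endurance has its plain meaning, the capacity to sustain effort, and that the tests are carried out as items 2 and 7 describe. It does not depend on the content of the national standard. Nor does it require that the intervention was aimed at cardiorespiratory endurance; Table 1 gives an exercise intensity but names no target component.

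**What to change.** In section 3.6, report vital capacity as lung function and make the 800/1000 m run the indicator of cardiorespiratory endurance. Remove muscular endurance as the label for the run.

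Then make the lists in 3.3 and 3.6 agree. If agility is tested, name the test and describe it; if it is not, delete the word from 3.3. Give the standing long jump a component.

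The relabelling is a change of wording only: it adds or drops no test and leaves the sample size and the analysis as they are. The downside is that the run can no longer be presented as a muscular endurance result, so that component either goes from the list or needs another of the existing tests to support it. If agility turns out not to be tested, no statement on agility can be made.

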3.7 Psychological Indicators

Health behaviors and sports ethics are assessed using [name] "Core Competency Evaluation Scale for Primary School Physical Education and Health." Depression symptoms are measured using the "Depression Scale from the Center for Disease Control."

3.8 Metabolomics Method

Forty students were randomly selected (20 from the experimental group and 20 from the control group). Urine samples (15 ml) were collected from these students before instruction, after the first session of instruction, and after 12 weeks of instruction. The samples were processed and analyzed using non-targeted metabolomics based on liquid chromatography–mass spectrometry (LC-MS) to identify differential metabolites before and after a single session of instruction, as well as before and after long-term instruction. Metabolic pathway analysis was also conducted to obtain metabolic fingerprints before and after the intervention.

Principal component analysis (PCA) and orthogonal partial least squares discriminant analysis (OPLS-DA) were employed to elucidate the differences in metabolic profiles before and after the intervention. Differential metabolites were further screened using t-tests of intragroup mean metabolite concentrations, OPLS-DA, and clustering analysis. The mass-to-charge ratios (m/z) of the metabolites were matched and analyzed against the Human Metabolome Database and the Kyoto Encyclopedia of Genes and Genomes (KEGG) database for structural identification, enrichment, and topological analysis of the differential metabolites. This approach was used to explore the metabolic pathways involved in the differential metabolites before and after a single session of instruction, as well as before and after long-term instruction, under the Healthy Physical Education Curriculum Model of China.

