3.5 Experimental Procedure

Informing the research process and precautions—Grouping by class—Pre-instruction testing (including physical health indicators, mental health indicators, and metabolite collection)—Testing after the first session of instruction (metabolite collection only)—Conducting 12 weeks of physical education instruction (experimental groups adopting the Chinese Healthy Physical Education Curriculum Model, control groups adopting traditional physical education instruction)—Post-instruction testing (consistent with pre-instruction testing).

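### Metabolites are selected by within-group before-after tests and read as effects of the curriculum, with no stated comparison of change between the arms

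*Protocol*

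**What the plan says.** **Sampling (Protocol 3.8).** "Forty students were randomly selected (20 from the experimental group and 20 from the control group"), with urine taken before instruction, after the first lesson and after 12 weeks. A concurrent control sample therefore exists at every time point.

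**Contrast (3.8).** The assay is meant "to identify differential metabolites before and after a single session of instruction, as well as before and after long-term instruction". PCA and OPLS-DA "were employed to elucidate the differences in metabolic profiles before and after the intervention".

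**Selection (3.8).** "Differential metabolites were further screened using t-tests of intragroup mean metabolite concentrations, OPLS-DA, and clustering analysis". The selected metabolites are matched to the two named databases, and the section closes by exploring their pathways under the new curriculum model.

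**Other indicators (3.10).** "Paired sample t-tests will be used to compare differences before and after intervention for each indicator". The next sentence adds: "Independent sample t-tests will be used to compare baseline indicators between the two groups and differences between the pre- and post-intervention values".

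**After the first lesson (3.5).** "Testing after the first session of instruction (metabolite collection only").

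**The concern.** A before-after change in the experimental classes is the sum of whatever the new curriculum does and whatever would have happened anyway. Section 3.4 gives both arms the same sport, lesson length and frequency, so a metabolite that responds to any volleyball lesson can move in both. Section 4.2 places the fieldwork between September and January, which leaves room for growth and season. The control urine could separate these sources, but the stated selection rule does not use it for that.

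What is at stake is the study's stated novelty. The Background says that the internal mechanisms of the model have not been reported, and the Research Objective makes metabolic mechanisms an aim. Followed as written, section 3.8 could report a pathway as the curriculum's mechanism when the control students changed just as much.

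**Working it through.** Section 3.8 gives no figure to reproduce. The sample size of 64 in the participants section rests on a two-group t-test and does not bear on this point. The check asks how often the stated rule would select a metabolite on which the curriculum has no effect.

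**Inputs from the documents**
- 20 students per arm (3.8).
- Significance at 0.05 (3.10). The documents do not state sidedness; two-sided is assumed.

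**Assumptions, not in the documents**
- Both arms have the same true mean change. It is expressed as dz, the mean change divided by the standard deviation of the change, and ranges from 0 to 1.0.
- The curriculum effect is zero.
- Changes are normal and independent between students, with no class effect.
- The within-group t-test is paired. Section 3.8 does not say so, but section 3.10 uses paired tests for before-after comparisons.

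**Within-group test, experimental arm**

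Degrees of freedom are 20 − 1 = 19 and the critical value is t = 2.093. The noncentrality is λ = dz × √20. With F the noncentral t distribution function,

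P(flagged) = 1 − F(2.093; 19, λ) + F(−2.093; 19, λ).

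**Between-arm test of change, 20 against 20**

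The common change cancels, so the rejection rate should equal the nominal 5%. A simulation with 100,000 runs per row confirms this.

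| dz in both arms | λ | Flagged by within-group test | Flagged by between-arm test (simulated) |
|---|---|---|---|
| 0 | 0 | 5.0% | 5.0% |
| 0.2 | 0.894 | 13.6% | 5.0% |
| 0.5 | 2.236 | 56.5% | 5.0% |
| 0.8 | 3.578 | 92.4% | 5.1% |
| 1.0 | 4.472 | 98.9% | 5.0% |

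**What the between-arm test can detect**

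For a true difference in change of 0.5 SD, λ = 0.5 × √(20/2) = 1.581 on 38 degrees of freedom, and two-sided power is 33.8%. Whole classes are assigned, three per arm, so an allowance for class would lower this further.

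The figures are per metabolite and cover the t-test step only. Section 3.8 does not say how the t-tests, OPLS-DA and clustering combine into one decision.

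**The case against.** **The control arm is used elsewhere.** A reader might infer that the pre-post results as a whole ignore the control arm. The documents do not support that. Section 3.10 follows its paired tests with independent-sample t-tests on the pre-post differences, most naturally a between-group test of change. The wording is loose, since the two groups are named only next to baseline, but paired tests reported beside such a test are not an error. This objection stands in full for the physical and mental health indicators.

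**Section 3.10 might cover metabolites too.** It mentions neither metabolites nor the sample after the first lesson, while section 3.8 is the specific rule for selecting metabolites. This does not remove the point.

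**Only the t-tests are called intragroup.** That is correct. The PCA and OPLS-DA sentence does not say whether the arms are modelled separately or together, and a statistical analysis plan that is not shown may settle it. Still, the contrast given is before against after, and the protocol itself fixes an intragroup t-test, so this is more than a detail left for later.

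**Attribution by comparing lists.** A reader might infer that a metabolite will be credited to the curriculum when it is significant in the experimental arm and not in the control arm. With equal true changes of 0.5 that pattern has probability 0.565 × 0.435 = 24.6%, but at 1.0 it falls to 0.989 × 0.011 = 1.1%. Neither section states such a rule, so these figures do not measure this plan.

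**Interference is addressed.** Section 3.3 uses questionnaires on activity, diet and sleep to deal with metabolic interference. These help, but they capture neither growth, nor season, nor the response to an ordinary lesson.

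**The substudy is exploratory.** Sections 3.3 and 3.8 do speak of exploring. That limits the weight of the results, but it does not make an uncontrolled change attributable to the curriculum.

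**Conclusion.** The point holds for the metabolomics in section 3.8 and only there. As written, the rule can select changes common to both arms and present their pathways as belonging to the curriculum model. Under the stated assumptions the false-attribution rate per metabolite rises from 13.6% to 98.9% as the common change goes from 0.2 to 1.0 SD, where a between-arm test would hold it near 5%. How large common changes will be is unknown, so the range matters more than any single value. The 5% also presumes that class is allowed for or has no effect.

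A secondary inconsistency is real but smaller. The Research Objective speaks of the effect of one-time teaching on physical and mental health, yet section 3.5 collects only metabolites after the first lesson. That part of the objective has no physical or mental health data behind it.

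**What to change.** 1. In section 3.8, state that metabolites attributed to the curriculum are selected on the between-arm difference in change, once for baseline to after the first lesson and once for baseline to week 12, allowing for class. Whether to use log change or to adjust for baseline is a choice among several; fix it before the data are analysed.
2. Interpret pathways as curriculum effects only for metabolites selected in this way.
3. Label the intragroup t-tests and any before-after PCA or OPLS-DA as descriptive.
4. Limit the one-time teaching objective to metabolites.

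No further urine is needed, because the control samples are already planned. The cost is in yield: fewer metabolites will pass, and power is only about 34% for a 0.5 SD difference in change, before any allowance for class. The mechanism results should therefore be called exploratory, and a metabolite that is not selected should not be read as unaffected.
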